### Sensorimotor deficits

Static balance will be estimated through the Time-In-Balance Test (TIBT). In the TIBT, participants will stand on a firm surface in a single-legged stance. Participants will be instructed to put their hands on their spina iliaca. The time taken to keep balance with eyes closed will be recorded and referenced with a cutoff score of 25.89 s [57]. The maximum duration of the test is 60-s [58]. The test will be carried out with 1 practice trial and 2 measured trials with a 60-s interval between each test. The longest time between the two tests will be recorded as the final score. The outcome will be discarded and replaced by a new test if: (1) participants move the tested foot; (2) the contralateral foot touches the floor.

Dynamic balance will be assessed using the Star Excursion Balance Test (SEBT), which is an effective means for determining reach deficits of CAI individuals [59]. There will be 8-direction including anterior, anteromedial, medial, posteromedial, posterior, posterolateral, lateral and anterolateral in the SEBT test. During the test, participants will be asked to stand at the center point using the involved limb and put their hands on their spina iliaca. Then, participants will be asked to use non-stance limb to reach in each direction as long as possible. In each direction, the farthest point of the great toe will be marked and recorded. The score will be discarded under the following conditions: (1) participants shift or lift the involved limb; (2) balance can not be maintained during the test. Before the official test, participants will have 2 practice trials to familiarize them with the test procedure and setting. To calculate the final SEBT score, the length of the lower limb measured from the anterior–superior iliac spine to the medial malleolus at the supine position will be used to divide the reach distance using the method described previously [60]. Besides, changes in SEBT scores will be examined to see if they reach the minimal detectable change in eight directions, including 6.73% (medial), 8.56 (anterior), 8.68 (anteromedial), 9.69 (anterolateral), 12.17 (lateral), 13.00 (posterior), 13.33 (posterolateral) and 13.36% (posteromedial) [61].

Proprioception will be evaluated by the Active Movement Extent Discrimination Apparatus (AMEDA). The AMEDA was designed to test the acuity of proprioception and it has been demonstrated to have good reliability and validity [62]. During the AMEDA test, one of 4 angles (10◦, 12◦, 14◦, and 16◦) of ankle inversion slope will be randomly generated for judgment. The Ankle Inversion Discrimination Apparatus for Landing (AIDAL), which has been determined to have higher ecological validity in assessing proprioception [63], will also be employed to assess ability to distinguish ankle inversion in landing tasks. Participants will be required to stand on the set-off platform with their eyes watching forward and then step off to land on a platform with one of four possible slopes (10◦, 12◦, 14◦, 16◦). Before the proprioception test, participants will be allowed to practice 4-time to enable them to remember the position sense associated with each slope. The formal session of tests, carried out by a blinded assessor using the random sequence, includes 40 trials (10 times for each angle at 10◦, 12◦, 14◦, 16◦) in AMEDA and AIDAL.

The isometric strength will be assessed using a hand-held dynamometer (precision 0.05%, input ± 15mv, measurement range -500 ~ 500N, Daysensor DY920, China), which has been tested as a reliable and valid tool in assessing isometric strength [64, 65]. It will be utilized to assess isometric strength in directions including inversion, eversion, dorsiflexion, and plantar flexion of the ankle joint. Each direction will be tested 2 times with a 60-s interval to obtain the average value for final analysis. Before strength measurement, all participants will be asked to be in a relaxed position. To ensure precision, the pelvis will be strapped onto the treatment bed.

In this study, functional performance will be estimated by the Side-Hop Test, described in another study [66]. All participants will be requested to hop 10 times (20 jumps together) across a 30 cm line as fast as possible. Before the formal test, they will be provided a chance to practice. This test will be conducted twice with a 3-min interval.

A handheld stopwatch will be used to record the time taken in the test. The faster result between the two formal tests will be selected as the final score. In addition, participants will be asked to report their degree of instability of the ankle joint (0–10 scale) during the test process.

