### Outcome measures

Sociodemographic information including name, sex, age, dominant leg, physical activity and level of kinesiophobia will be collected through online questionnaires. Self-reported measures consist of the CAIT and FAAM. Objective measures in the current study include sensorimotor function and brain plasticity. The primary outcome measures will be balance with SEBT end-point to determine sensorimotor deficit, and activation of brain area with oxyhemoglobin in determining brain plasticity. All measures of outcome will be performed by a qualified blinded assessor, who is independent of the current study, at the fitness laboratory of Zhejiang University. An adequate rest period, assessed with a rating of perceived exertion (Borg scale, 6–20), will be given between each of the two objective measures to avoid potential fatigue. Since TMS is potentially associated with alterations of functional performance, the test orders (Table 2) will be arranged to mitigate any mutual influence between each two tests. To avoid the influence of myopia on balance control, participants will be asked to wear any corrective eyewear throughout the test process. The extremity with the lower CAIT score will be tested if bilateral ankle instability exists. Outcome measures will be assessed before and after the WBV intervention. According to a previous study, there were delayed improvements in balance and self-reported functions for patients with CAIafter accepting balance training programs [56]. Hence, the follow-up assessments will be performed 2-week after the intervention program.

**Table 2 Tab2:** SPIRIT timetable including schedule of enrolment, interventions and assessments

	Study period					
	Enrolment	Baseline assessment	Allocation	Post-allocation	Post-intervention assessment	Follow-up
Time points	-4 to -1 weeks		0	1–6 Weeks	6–7 weeks	8–9 Weeks
Enrollment						
Eligibility screen	X					
Informed consent	X					
Random allocation			X			
Intervention						
WBV						
Assessment						
Primary outcome measures						
Brain activity						
Corticomotor Plasticity (TMS)		X			X	X
Activation of brain area (fNIRS)		X			X	X
Sensorimotor deficits						
Balance (SEBT&TIBT)		X			X	X
Strength (HHD)		X			X	X
Proprioception (AMEDA)		X			X	X
Functional performance (SHT)		X			X	X
Secondary outcome measures						
Ankle instability (CAIT)		X			X	X
Ankle function (FAAM)		X			X	X

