
Functional near-infrared spectroscopy (fNIRS) is a technique used to investigate patterns of cortical brain activation [71]. In this study, fNIRS will be implemented to investigate any alteration of functional plasticity after the WBV intervention. Oxyhemoglobin of the postcentral gyrus, the precentral gyrus, and the supplementary motor area will be recorded by the fNIRS system (NIRS Sport, NIRx Medical Technologies LLC, USA). In this system, there are 20 channels composed of 8 sources and 8 detectors. Two sorts of wavelengths, including 695 and 830 nm, and a frequency of 10 Hz will be adopted in the process of sampling data. The electrodes will be distributed to the targeted area according to the international 10/20 system. Positional information about each electrode will be obtained using a 3-dimensional digitizer (FASTRAK; Polhemus, Colchester, VT, USA) with 4 reference points (i.e., nasal root, parietal, left preauricular, and right preauricular) [13]. Before the formal test, participants will be given verbal instructions and a chance to familiarize themselves with the device. After this process, they will be asked to sit in the chair for 60 s to collect baseline cortical activity. Then, participants will stand with the involved leg on a firm surface and keep their hands on their hips. A sample lasting for 60 s will be conducted when standing with eyes opened and closed respectively. The interval between trials will be set at 60-s. Any recording during which participants lose their balance (e.g., removing hands from hips, shifting the feet, and touching the ground with the opposite limb) will be discarded, and retested until successful trials are obtained.

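### The Time-In-Balance Test discards and repeats trials that end in a foot movement or touch-down, the main failures it should time, which pushes kept scores toward the 60-s ceiling

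*Protocol article*

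**What the plan says.** The rule is in the protocol article, Sensorimotor deficits, in the paragraph on static balance. The quantity measured is stated first: "The time taken to keep balance with eyes closed will be recorded and referenced with a cutoff score of 25.89 s". A cap follows: "The maximum duration of the test is 60-s". Then come the number of trials, "The test will be carried out with 1 practice trial and 2 measured trials with a 60-s interval between each test", and the summary score, "The longest time between the two tests will be recorded as the final score". The paragraph closes with the discard rule: "The outcome will be discarded and replaced by a new test if: (1) participants move the tested foot", with floor contact of the other foot as condition (2).

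The paragraph names no event that stops the watch and no maximum number of repeats.

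Two other places bear on the point. Under Brain plasticity, the fNIRS stance recordings are repeated when participants "lose their balance (e.g., removing hands from hips, shifting the feet, and touching the ground with the opposite limb". Under Outcome measures, Table 2 has the row "Balance (SEBT&TIBT" beneath its primary heading, while the text of the same section names the SEBT alone as the primary balance end-point.

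**The concern.** The TIBT is a time-to-failure measure. A participant stands on one leg with eyes closed until balance goes, and the elapsed time is the result. The two events that lead to a discard are the obvious ways in which single-leg balance is lost. A discard rule suits the SEBT, where a failed reach is not a valid reach, and the fNIRS recording, which needs an undisturbed 60 s. For a test whose result is the time of failure, it deletes the observation itself.

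At stake is the article's only test of static balance. Scores pressed against a ceiling lose the spread that the planned ANOVA and the planned Pearson correlation with brain measures need, and a baseline deficit relative to 25.89 s becomes hard to see. Weaker balancers would also make more attempts than stronger ones before two trials are kept, so the testing itself would differ with the trait being measured.

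**Working it through.** **1. The passages side by side.** The score is time in balance. The cap of 60 s, the 25.89-s cutoff and the longest-of-two rule all presuppose that trials shorter than 60 s are kept. The discard rule removes trials with a stance-foot movement or a touch-down. The fNIRS section gives three examples of losing balance: hands leaving the hips, feet shifting, and the opposite limb touching the ground. Two of the three are the TIBT discard events. A TIBT score below 60 s can therefore come only from an end event that the TIBT paragraph does not name, such as a hand lifting or the eyes opening.

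**2. Sample size.** No TIBT figure enters it. The stated 64 reproduces as a repeated-measures ANOVA, between factors, with effect size 0.35 taken as Cohen's f, four groups, three measurements and an assumed correlation of 0.5 (power 0.805 at 64). Then 64 / (1 − 0.20) = 80. Nothing here changes.

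**3. Illustration of the effect on scores.** The article gives no distribution of hold times. Assume exponential times to the end of a trial with median m, independent attempts, and a share q of the endings before 60 s that are foot movements or touch-downs. Medians of 15, 25.89 and 40 s are tried. The 25.89 is borrowed from the cutoff only as a convenient value; a cutoff is not a median.

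- Chance of reaching 60 s in one attempt: p = 2^(−60/m)
- Chance that an attempt is kept under the written rule: k = p + (1 − p)(1 − q)
- Share of kept trials at 60 s: s = p/k
- Share of best-of-two scores at 60 s: 1 − (1 − s)²
- Expected attempts for two kept trials: 2/k
- If failures are scored instead, the share at 60 s is 1 − (1 − p)²

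Example, m = 25.89 and q = 0.9: p = 2^(−2.318) = 0.201; k = 0.201 + 0.799 × 0.1 = 0.281; s = 0.715; share at 60 s = 1 − 0.285² = 0.92; attempts = 2/0.281 = 7.1.

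Share of best-of-two scores at 60 s, with expected attempts in brackets:

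| Median m | p | Failures scored | Written rule, q = 1 | q = 0.9 | q = 0.67 |
|---|---|---|---|---|---|
| 15 s | 0.0625 | 12% | 100% (32) | 64% (12.8) | 31% (5.4) |
| 25.89 s | 0.201 | 36% | 100% (10.0) | 92% (7.1) | 68% (4.3) |
| 40 s | 0.354 | 58% | 100% (5.7) | 98% (4.8) | 86% (3.5) |

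Mean best-of-two score in seconds, by simulation under the same assumptions:

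| Median m | Failures scored | q = 1 | q = 0.9 | q = 0.67 |
|---|---|---|---|---|
| 15 s | 29.8 | 60.0 | 47.6 | 36.2 |
| 25.89 s | 41.8 | 60.0 | 57.6 | 50.8 |
| 40 s | 49.4 | 60.0 | 59.4 | 56.4 |

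**4. Effect on a contrast.** Between medians of 25.89 and 40 s, the difference in means is 49.4 − 41.8 = 7.6 s when failures are scored. Under the written rule it is 0 s (q = 1), 59.4 − 57.6 = 1.8 s (q = 0.9) or 56.4 − 50.8 = 5.6 s (q = 0.67). Between medians of 15 and 25.89 s, it is 41.8 − 29.8 = 12.0 s when scored, against 0, 10.0 and 14.6 s. Scores always move up, but the contrast does not always shrink; it depends on q and on where the groups lie.

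**The case against.** The strongest reply is that this is a slip of wording. The cutoff, the cap and the longest-of-two rule show that shorter trials are meant to count, the procedure is cited to earlier studies, and an assessor may well stop the watch at touch-down. A small shift of the stance foot could also be meant as a technical fault. This supports a benign intention, but it does not rescue the printed rule: touch-down of the other foot is plainly a loss of balance, and an assessor who scores it departs from the protocol. The article gives an explicit instruction here, so this is not a detail left to a fuller document.

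Three stronger readings are tempting and are not supported.

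- **Every score will be 60 s and arms cannot differ.** That needs foot movement and touch-down to be the only endings. The test also requires hands on the iliac spines and closed eyes, and the fNIRS section counts hands leaving the hips as loss of balance, so some shorter scores may survive.
- **A primary end-point is invalidated.** Table 2 groups nearly all objective tests under its primary heading, but the text names the SEBT as the primary balance end-point. The other sensorimotor measures and fNIRS remain available for the correlation analysis.
- **Extra attempts bias the comparison between arms.** More attempts for weaker balancers follow from the rule. Fatigue is partly met by the 60-s interval, and a difference by arm is conjecture.

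The modelled percentages rest on assumed inputs and carry no weight beyond illustration.

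**Conclusion.** The point stands as a contradiction within one paragraph. The TIBT score is the time to loss of balance, and the written discard rule removes and repeats the trials that end in the main forms of that loss. Kept scores are biased upward toward 60 s: all of them are at 60 s if the two listed events are the only endings, and fewer if other endings occur. Under the assumed exponential model with a median of 25.89 s, the share at the ceiling goes from 36% to 68%, 92% or 100% as the listed share of endings goes from 0.67 to 0.9 to 1. The direction does not depend on that model; the size does. The damage is confined to the static-balance outcome.

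**What to change.** Replace the discard sentence with a scoring rule along these lines: timing stops at the first loss of balance or of test position, namely movement of the tested foot, floor contact of the other foot, hands leaving the iliac spines, or eyes opening; the elapsed time is the trial score; a trial with none of these by 60 s scores 60 s. Hands and eyes need to be in the list, since otherwise a participant who opens the eyes early and stays standing would be credited with 60 s. Allow discard and repeat only for procedural faults, such as an outside disturbance or a stopwatch error. Keep the two measured trials and the longest-time rule.

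The cost is one or two sentences in the protocol and the assessor instructions, with no added visits, staff or participants. Trial status gives 1 May 2023 as the start of enrolment, before the article's publication on 18 July 2023. The sponsor should therefore also establish how any TIBT trials already done were scored and whether the times of discarded attempts were written down, because unrecorded times cannot be recovered.

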### Brain plasticity

In the present study, transcranial magnetic stimulation (TMS) will be used to assess corticomotor alterations including cortical excitability, corticospinal inhibition, and representation of muscles. Single magnetic pulses (max 4 Tesla) will be delivered to the cortical representation of the lower leg muscles by a double-cone coil with TMS equipment (PowerMAG, Mag&More Inc., Germany). All participants will wear an elastic cap and sit on the chair with a relaxed lower limb. A wireless electrode of Delsy’s sEMG system (Trigno, Delsys Inc., Natick, MA, USA) will be placed on the muscle belly of the tibialis anterior and peroneus longus to collect the motor evoked threshold (MEP). The surface of these muscles will be shaved and cleaned with alcohol-impregnated tissues prior to electrode placement. The EMG signal will be collected at a sample rate of 2000 Hz and analyzed using the Matlab software (Matlab 2022a, MathWorks Inc., Natick, USA) with band-pass filters (high-pass of 10 Hz and low-pass of 500 Hz). Prior to the official test, the familiarization procedure will be conducted to reduce any apprehension caused by the magnetic stimuli. The method of identifying a hot spot will be in line with the one reported in a previous study [67]. The double-cone coil will be moved and delivers pulses (70% of magnitude, 5-s interval) to the vertex of the skull. The hot spot will be identified and marked until the maximum peak-to-peak MEPs (50 μV) are found. Subsequently, the stimulation magnitude on the hot spot decreases by 50% until MEP will not be elicited, and then increases by 1%. Rest motor threshold (RMT) will be defined as the stimulation magnitude by which 5 out of 10 pulses generate MEP > 20 μV [18]. Active motor threshold (AMT) will be defined as the least MEP intensity eliciting peak-to-peak MEP amplitude ≥ 100 μV in 5 out of 10 pulses. RMT and AMT will be presented as the percentage of maximum Tesla [68]. Corticospinal inhibition will be represented by the cortical silent period (CSP). According to previous studies, the CSP has been defined as the distance from the end of the MEP to the return of the mean EMG signal plus two times the standard deviation of the baseline EMG signal [69, 70]. The map area and the volume of cortical representation in the peroneus longus and anterior tibialis, which are used to represent an expansion of the cortical representation and the total excitability of cortical representation respectively, will be calculated by referring to the method reported previously [12]. All results in the TMS test will be collected in each group and used for statistical analysis.

Functional near-infrared spectroscopy (fNIRS) is a technique used to investigate patterns of cortical brain activation [71]. In this study, fNIRS will be implemented to investigate any alteration of functional plasticity after the WBV intervention. Oxyhemoglobin of the postcentral gyrus, the precentral gyrus, and the supplementary motor area will be recorded by the fNIRS system (NIRS Sport, NIRx Medical Technologies LLC, USA). In this system, there are 20 channels composed of 8 sources and 8 detectors. Two sorts of wavelengths, including 695 and 830 nm, and a frequency of 10 Hz will be adopted in the process of sampling data. The electrodes will be distributed to the targeted area according to the international 10/20 system. Positional information about each electrode will be obtained using a 3-dimensional digitizer (FASTRAK; Polhemus, Colchester, VT, USA) with 4 reference points (i.e., nasal root, parietal, left preauricular, and right preauricular) [13]. Before the formal test, participants will be given verbal instructions and a chance to familiarize themselves with the device. After this process, they will be asked to sit in the chair for 60 s to collect baseline cortical activity. Then, participants will stand with the involved leg on a firm surface and keep their hands on their hips. A sample lasting for 60 s will be conducted when standing with eyes opened and closed respectively. The interval between trials will be set at 60-s. Any recording during which participants lose their balance (e.g., removing hands from hips, shifting the feet, and touching the ground with the opposite limb) will be discarded, and retested until successful trials are obtained.

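### Eyes-closed fNIRS recordings count only after an unbroken 60-s single-leg stance, with unlimited retests, so if they enter the primary oxyhemoglobin outcome, their availability and timing depend on the balance being treated

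*Protocol article*

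**What the plan says.** Outcome measures names two primary outcomes: the Star Excursion Balance Test and "activation of brain area with oxyhemoglobin in determining brain plasticity". It does not say whether the eyes-open recording, the eyes-closed recording or both supply that value.

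Brain plasticity describes the fNIRS task. After one 60-s seated baseline, "participants will stand with the involved leg on a firm surface and keep their hands on their hips". Then: "A sample lasting for 60 s will be conducted when standing with eyes opened and closed respectively". Also: "The interval between trials will be set at 60-s". The acceptance rule covers both conditions: "Any recording during which participants lose their balance" (the examples are hands leaving the hips, the feet shifting, or the other limb touching the ground) "will be discarded, and retested until successful trials are obtained". This is a stated rule with no stopping point.

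Sensorimotor deficits describes the Time-In-Balance Test (TIBT): "participants will stand on a firm surface in a single-legged stance", with hands on the iliac spines. "The time taken to keep balance with eyes closed will be recorded and referenced with a cutoff score of 25.89 s". The test ends at 60 s.

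**The concern.** The eyes-closed fNIRS task and the TIBT are nearly the same stance: one leg, firm surface, hands at the pelvis, eyes closed. On the TIBT, 60 s is the best possible score. For fNIRS it is the minimum for a recording to be kept. Retention of the eyes-closed signal is therefore conditional on an ability that the interventions are meant to improve, in participants enrolled for instability.

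If eyes-closed data enter the primary oxyhemoglobin outcome, two things come to depend on balance. One is whether a value exists at all. The other is how many attempts preceded the retained recording, and so how much practice, possible fatigue and elapsed time since the single seated baseline it carries. Both can differ by arm and by visit if training works. What is at stake is the between-arm oxyhemoglobin contrast and the correlation between brain change and sensorimotor change, which is the trial's second research question. Part of that correlation could come from the measurement rule.

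**Working it through.** **1. Tasks side by side.** TIBT: single leg, firm surface, hands on iliac spines, eyes closed, reference 25.89 s, maximum 60 s. Eyes-closed fNIRS: involved leg, firm surface, hands on hips, 60 s required. Required hold relative to the cutoff: 60 / 25.89 = 2.32.

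**2. Success per attempt (illustration).** The article gives no hold-time distribution. Assume that the cutoff is the typical hold time and that attempts are independent. Let p be the probability of holding 60 s; expected attempts are 1/p.

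- Exponential, median 25.89 s: p = 2^(−60/25.89) = 0.20, about 5 attempts; within five attempts 1 − 0.799^5 = 0.67 succeed.
- Exponential, mean 25.89 s: p = exp(−60/25.89) = 0.10, about 10 attempts; 0.41 succeed within five.
- Lognormal, median 25.89 s, log-SD s: p = 1 − Φ(ln(2.32)/s). For s = 0.4, p = 0.02 (about 56 attempts); for s = 1.0, p = 0.20 (about 5 attempts).

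With the median at the cutoff, p runs from about 0.02 to 0.20 and expected attempts from about 56 down to 5. The width of that range shows that the size is not identified.

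**3. How arms could diverge.** If training moved p from 0.10 to 0.20 while control stayed at 0.10, expected attempts at post-test would be 5 against 10. Whether attempt number shifts oxyhemoglobin, and in which direction, cannot be derived from the article.

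**4. Sample size.** The stated 64 reproduces. For the between-groups test in a repeated-measures ANOVA, λ = f²·N·m / (1 + (m − 1)ρ), with f = 0.35, m = 3, four groups and ρ = 0.5 (assumed; not stated). At N = 64, λ = 0.1225 × 64 × 3 / 2 = 11.76 and power is 0.80. Then 64 / 0.8 = 80. This point does not dispute either figure. Only if the primary value required a valid eyes-closed recording would losses matter here: a further 10%, 20% or 30% missing from 64 leaves 57, 51 or 44 and power of about 0.75, 0.69 or 0.61.

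**5. What an early window would achieve (illustration, exponential).** Probability of no usable recording after three attempts:

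| Median hold | 60 s required | 20-s window | 10-s window |
|---|---|---|---|
| 25.89 s | (1 − 0.201)³ = 0.51 | (1 − 0.585)³ = 0.07 | (1 − 0.765)³ = 0.01 |
| 10 s | (1 − 0.016)³ = 0.95 | 0.75³ = 0.42 | 0.50³ = 0.13 |

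The window reduces the selection without removing it.

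**The case against.** **Eyes-open data survive.** A reader might infer that anyone who fails eyes closed has no primary fNIRS value. The article does not support that: it records both conditions and does not make eyes closed the primary one. No reference time is given for eyes open. The six-week programme (Table 1) prescribes 60-s one-legged stances on foam or BOSU from the first week, so the design treats a 60-s single-leg stance as achievable, although eyes closed is not mentioned there. This objection stands and limits the point to the case where eyes-closed data feed the primary outcome.

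**The cutoff is not a typical hold time.** A reader might infer from 25.89 s that many participants cannot manage 60 s. The article does not say what the cutoff separates and gives no mean, median or spread. The share who would fail is unknown. This stands.

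**Fatigue is not shown.** Failed attempts may be short and each is followed by 60 s of rest. Fatigue is therefore a possible effect and not an established confounder. However, the rest guided by perceived exertion is specified between measures and not for repeats within fNIRS, so the risk is uncontrolled.

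**Discarding falls has a purpose.** It makes every retained recording cover the same completed task. That is legitimate, but it does not answer the dependence on balance.

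**A cap and fallback could sit in a fuller protocol.** Their mere absence from an article would be no finding. Here, however, the article states the opposite of a cap: repeat until success. Followed as written, that rule produces the dependence.

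**Conclusion.** The point holds in conditional form. The article fixes an acceptance rule that, for the eyes-closed recording, demands maximum TIBT performance and allows unlimited retries, and it leaves open whether that recording is part of a primary outcome. If it is, availability and attempt number depend on the treated ability and can bias the arm contrast and the brain-balance correlation. The direction and size of any bias are unknown. Success rates of about 2% to 20% per attempt rest on an assumed median at the cutoff, assumed distribution shapes and independent attempts; they are illustrations, not estimates. The sample size is unaffected unless eyes-closed validity defines the primary value. This should be fixed; because eyes-open values remain, it does not by itself invalidate the primary fNIRS outcome.

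**What to change.** 1. Name the eyes-open recording as the primary fNIRS condition and the eyes-closed recording as supportive.
2. For eyes closed, retain the signal from stance onset to first loss of balance and analyse a pre-specified early window (for example 10 to 20 s) instead of discarding the recording.
3. Replace the open-ended retest rule with a fixed maximum number of attempts (for example three).
4. Log the number of attempts for both conditions and report it by arm and visit.
5. Check whether the fNIRS contrast and the brain-balance correlation are sensitive to attempt number.

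The cost is protocol wording, a processing window and one logged count; no new visit or equipment is needed. The downsides are a shorter eyes-closed signal and some remaining missing data in participants who lose balance before the window ends. The change is best made early, because discarded signals and uncounted attempts may not be recoverable later.
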